#### Research question 4: participant/caregiver perceptions

Key themes will be identified from the semistructured interviews in the nested qualitative study to improve our understanding of participants’ perspectives about research participation and randomization, and their assessment experiences. The analysis will be guided by the framework approach [65].

#### Research question 5: effect size

The measures described below will be used with the adults with Down syndrome at baseline and after 12 months of simvastatin or placebo treatment to determine the effect size by comparing the simvastatin group with the placebo group.

The primary outcome measure will be cognitive decline (using the instruments outlined above) [53,60-64]. The secondary outcomes will be measured using the following instruments:

1. American Association on Intellectual and Developmental Disabilities Adaptive Behavior Scale (to measure the adaptive function of persons with intellectual disabilities) [66]

2. Townsend’s Disability Scale (to measure general health) [67]

3. EQ-5D (the EuroQol 5-Dimension Questionnaire; to measure health outcomes and quality of life) (recently reviewed for use with people with intellectual disabilities [68])

4. Client Service Receipt Inventory (to measure demographics and extent of service use as well as social changes, such as changes in level of paid support, move to a nursing home or loss of day placement) (This instrument was designed for use with adults with intellectual disabilities and adults with mental illness.) [69,70]

5. The 12-item General Health Questionnaire (to be given to the caregivers at baseline and after 12 months to compare the health and carer strain of caregivers of participants in the simvastatin group with caregivers of participants in the placebo group) [71].

#### Research question 6: biomarkers

At baseline and after 12 months of simvastatin or placebo treatment, blood will be taken to measure Aβ40/Aβ42 levels for comparison between the simvastatin and placebo groups.

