**Methods/Design:**

TOP-COG is a feasibility and pilot double-blind randomized controlled trial (RCT), with a nested qualitative study, conducted in the general community. About 60 Down syndrome adults, aged ≥50 will be included. The intervention is oral simvastatin 40mg at night for 12 months, versus placebo. The primary endpoint is recruitment and retention rates. Secondary endpoints are (1) tolerability and safety; (2) detection of the most sensitive neurocognitive instruments; (3) perceptions of Down syndrome adults and caregivers on whether to participate, and assessment experiences; (4) distributions of cognitive decline, adaptive behavior, general health/quality of life, service use, caregiver strain, and sample size implications; (5) whether Aβ42/Aβ40 is a cognitive decline biomarker. We will describe percentages recruited from each source, the number of contacts to achieve this, plus recruitment rate by general population size. We will calculate summary statistics with 90% confidence limits where appropriate, for each study outcome as a whole, by treatment group and in relation to baseline age, cognitive function, cholesterol and other characteristics. Changes over time will be summarized graphically. The sample size for a definitive RCT will be estimated under alternative assumptions.

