### Study aims

The aims of the study are (1) to acquire data to design a full-scale multi-center RCT of simvastatin for the primary prevention of dementia in AD, (2) to test recruitment and retention strategies to inform future trials with this population, (3) to determine the best instruments to use in future studies measuring cognitive decline in adults with Down syndrome and (4) to investigate mechanisms, using Aβ42/Aβ40 measurements as a putative surrogate biological marker. Additionally, consent will be obtained for subsequent future longer-term follow-up by record linkage to routinely collected health data and for samples to be banked at the University of Glasgow for potential future research.

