### Research questions

The research questions we will seek to answer are listed below.

1. What are the trial recruitment and retention rates and recruitment sources?

2. What are the rates of tolerability and safety of simvastatin 40 mg OD?

3. Which instruments are the most sensitive for detecting early cognitive decline with the least floor effect in adults with Down syndrome adults?

4. What are the perceptions of adults with Down syndrome and their caregivers regarding their decision whether to participate and be randomized and their assessment experiences?

5. What are the distributions of the primary outcome measure (cognitive decline) and key secondary outcome measures (adaptive behavior, general health and quality of life, service use and caregiver strain) that would be used in a definitive RCT, and what are the sample size implications of these distributions?

6. Is Aβ42/Aβ40 a biomarker for cognitive decline?

7. Do the results support proceeding to a full RCT?

The outcome measures we will use to answer each of the research questions listed above are described in the subsections that follow.

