#### Pilot randomized controlled trial

A detailed statistical analysis plan will be prepared prior to the unblinding to treatment allocations, according to the RCB/Glasgow Clinical Trials Unit standard operating procedures. Briefly, summary statistics will be presented, with 90% confidence limits where appropriate, for each study outcome as a whole, by treatment group and in relation to baseline participant characteristics. Changes in outcomes over time will be summarized and presented graphically. The treatment effect estimate is of interest, not so much in terms of the magnitude or statistical significance of effect (the sample size is too small to draw definitive conclusions in this study), but rather regarding the uncertainty in this estimate or the variability in the rate of cognitive decline from which this estimate is derived. It is this variability estimate that will inform the sample size for a definitive trial, along with information about likely recruitment and retention rates. Statistical results will be interpreted in terms of the implications for a definitive RCT; for example, the sample size (and cost) required for screening and randomization will be estimated under alternative assumptions based on the pilot data. In additional analyses, we will examine outcomes of cognitive decline in relation to age, ApoE status, baseline cognitive function, cholesterol level and other baseline characteristics, which may provide information useful in defining the target population in future studies. We intend to apply exploratory factor analysis and other data reduction methods to examine interrelationships between different cognitive measures and their changes over time. The data gathered will not be sufficient to propose alternative outcome measures based on this analysis, but we may be able to propose novel hypotheses to be tested in a larger study.

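### Research question 6 asks whether Aβ42/Aβ40 is a biomarker for cognitive decline, but its subsection states only a comparison of Aβ between arms, and no section explicitly relates Aβ to cognitive change

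*Protocol article*

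**What the plan says.** The Research questions section lists as item 6: "Is Aβ42/Aβ40 a biomarker for cognitive decline". The Abstract repeats it as the fifth secondary endpoint, "whether Aβ42/Aβ40 is a cognitive decline biomarker". Aim 4 under Study aims is worded differently: "to investigate mechanisms, using Aβ42/Aβ40 measurements as a putative surrogate biological marker".

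The Research questions section then tells the reader where to look: "The outcome measures we will use to answer each of the research questions listed above are described in the subsections that follow". The subsection headed Research question 6: biomarkers is a single sentence. At baseline and at 12 months, "blood will be taken to measure Aβ40/Aβ42 levels for comparison between the simvastatin and placebo groups". Cognition is not mentioned in it.

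Under Data analysis, Pilot randomized controlled trial, the protocol promises summaries of each outcome overall, by arm and against baseline characteristics. It adds that "we will examine outcomes of cognitive decline in relation to age, ApoE status, baseline cognitive function, cholesterol level and other baseline characteristics", and gives the purpose of that work as something "which may provide information useful in defining the target population in future studies". Aβ is not named anywhere in that section. A detailed statistical analysis plan is to follow and is not shown.

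**The concern.** Whether a marker is a biomarker for decline is a question about association across participants: do those with a particular Aβ42/Aβ40 value, or a particular change in it, decline more on the cognitive tests? A comparison of Aβ between simvastatin and placebo asks whether the drug alters the marker. The two questions can have opposite answers. The drug may leave Aβ untouched while Aβ predicts decline well, or it may shift Aβ while Aβ has no bearing on cognition.

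If the subsection is followed literally, the endpoint is not answered by the analysis attached to it. A null arm difference could then be reported as evidence against the marker, or a clear arm difference as evidence for it, and neither would follow. Because aim 4 presents the ratio as a possible surrogate, such a misreading could carry over into the choice of outcomes for later trials.

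**Working it through.** **Inputs.** The question, the endpoint, the aim and the stated comparison are as quoted above. The Statistical power section gives 50 participants with 12-month data and works with 90% confidence intervals. Research question 3 lists eight cognitive tests. The protocol gives no figure for Aβ, so there is no Aβ calculation to reproduce. (The figure from which the 50 is taken does reproduce: the chi-square 90% CI for a variance with 49 degrees of freedom has width 49/χ²(0.05) − 49/χ²(0.95) = 0.706 of the estimate, against the stated 70%. It has no bearing on this point.)

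**Step 1: what the arm comparison estimates.** Write Aβ change as δ·T + e and cognitive change as γ·T + u, where T is the treatment indicator and the within-arm correlation of e and u is ρ. The difference in mean Aβ change between arms has expectation δ and, in SD units with an assumed 25 completers per arm, standard error √(2/25) = 0.283. Neither expression contains ρ, and ρ is what question 6 asks about.

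**Step 2: check by simulation.** With 25 per arm and 4,000 runs, and with assumed values of δ and ρ:

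| Drug effect on Aβ (SD) | True ρ | Mean arm difference | SD of arm difference | Mean within-arm correlation |
|---|---|---|---|---|
| 0 | 0 | −0.01 | 0.28 | 0.00 |
| 0 | 0.6 | 0.00 | 0.29 | 0.60 |
| −0.8 | 0 | −0.81 | 0.28 | 0.00 |
| −0.8 | 0.6 | −0.80 | 0.28 | 0.60 |

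The arm difference is the same, to simulation error, whether the association is absent or strong. Only the within-arm correlation separates the two cases.

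**Step 3: does another section supply the association?**

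- The list in Data analysis is "cognitive decline in relation to age, ApoE status, baseline cognitive function, cholesterol level and other baseline characteristics". Aβ is measured at baseline, so baseline Aβ could be placed under the last item. It is not named, and the stated purpose is choosing a target population rather than assessing a marker.
- Change in Aβ over 12 months is not a baseline characteristic. No section links it to cognition.
- The general summaries of outcomes by arm and by baseline characteristics do not supply that link either.

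**Step 4: what the planned data could give.** For a single unadjusted correlation, the Fisher z 90% CI is tanh(atanh r ± 1.645/√(n − 3)). With n = 50 the half-width on the z scale is 1.645/√47 = 0.240.

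| Assumed r | atanh r | 90% CI for r |
|---|---|---|
| 0 | 0 | −0.24 to 0.24 |
| 0.3 | 0.310 | 0.07 to 0.50 |
| 0.4 | 0.424 | 0.18 to 0.58 |
| 0.5 | 0.549 | 0.30 to 0.66 |

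These intervals are wide but informative for a pilot. They assume complete Aβ data in all 50 and no covariates.

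**Step 5: multiplicity.** Eight tests with two Aβ predictors each give 8 × 2 = 16 associations. If none were real, the expected number of 90% intervals excluding zero would be 16 × 0.10 = 1.6.

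**The case against.** The strongest reply has four parts.

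- **The subsections are introduced as describing outcome measures, and analysis is left to a later plan.** This is true, and that plan may contain the association analysis. But the subsection does more than name a measure: it states the comparison the measure is for, and that comparison does not fit the question. This is a mismatch within the document, not detail left out for brevity.
- **Baseline Aβ against decline may already be covered by the list of baseline variables.** This is a fair reading and partly stands. A reader might infer from the biomarker subsection that the protocol excludes any analysis of Aβ against cognition; the documents do not support that. What remains uncovered is change in Aβ, together with any explicit statement for baseline Aβ.
- **The arm comparison is not a mistake.** This stands. Aim 4 concerns mechanism and a putative surrogate, and whether the drug moves the marker is a proper part of that. It should be kept, not replaced.
- **The precision figures flatter the remedy.** This also stands in part. The correlations are assumed, the intervals are for one unadjusted correlation, and there are eight tests. Not every completer need give venous blood twice: the exclusion criteria accept saliva for ApoE and capillary blood for cholesterol. Real intervals are likely to be wider.

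A reader might also infer that the ratio is inverted in the biomarker subsection, because the peptides appear there in the other order. That text speaks of levels and does not use the word ratio, so it may simply mean both peptides. The most it supports is a request to define the marker once.

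**Conclusion.** The point holds in limited form. The protocol attaches to question 6 and secondary endpoint 5 a comparison that cannot answer them, and no section explicitly relates Aβ to cognitive change. The arm contrast carries no information on that association; this follows from the algebra and does not depend on the assumed correlations. The illustrative CIs do depend on them, and on 50 participants with complete Aβ data.

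Severity is moderate. A reader might infer that the endpoint is lost or that the pilot's conclusions are at risk. The documents do not bear this out. The primary endpoint is recruitment and retention, the recommendation for a full trial under Research question 7 does not rest on Aβ, and the planned samples and test scores allow the association to be estimated. It would also be wrong to argue that the arm comparison will usually be null: under an assumed zero drug effect that only restates the size of the test.

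**What to change.** In the Research question 6 subsection:

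1. Keep the comparison of Aβ between arms and label it as the mechanism analysis for aim 4.
2. Add an exploratory analysis relating 12-month change on each of the eight cognitive tests to (a) baseline Aβ42/Aβ40 and (b) its 12-month change. Adjust for treatment arm and the baseline score on that test. Adjustment for arm matters for (b), since a drug effect on both variables would produce a pooled correlation with no link within arms.
3. Keep further covariates few at about 50 completers. Report estimates with 90% CIs and the number of participants contributing Aβ data.
4. State that results across the eight tests are exploratory and that a single interval excluding zero does not establish a biomarker.
5. Define the marker once as Aβ42/Aβ40 and use that form throughout.

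The cost is a few sentences of text, slightly more analysis, and the multiplicity noted above. No extra participants, visits or samples are needed beyond those already planned.

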#### Research question 7: recommendations for a full randomized controlled trial

1. The size of the general population pool needed to recruit adults with Down syndrome for the full RCT will be determined on the basis of the rates of recruitment and study completion in this pilot study, combined with the treatment effect estimate and uncertainty regarding the estimate. Additionally, the sensitivity of the neuropsychological measures will inform this decision, in particular with regard to the floor effect with persons with the most severe intellectual disabilities; in other words, to provide information about the proportion of the recruited population for whom it was possible to detect and measure change and therefore the likely proportion who would need to be excluded based on their baseline assessment of intellectual function.

2. This pilot study will consider the size of the geographical recruiting area required and hence the associated costs. The full RCT would not be appropriate if there were unexpected adverse safety effects identified in this pilot study, which we consider to be unlikely.

### Ethical considerations and consent

The study was given a favorable opinion by the Scotland A Research Ethics Committee (REC). In keeping with this response, each potential participant’s capacity to decide whether to participate in the trial will be assessed through discussion of the study, which will be facilitated with the person’s caregiver. This discussion with each potential participant will include going through the information sheet, which will be designed for persons with intellectual disabilities. The discussion will include what their participation will involve and will inform them that they will not benefit personally from taking part and that they do not have to participate if they do not wish to. Any questions that the person or caregiver has will be discussed and answered. To assess the person’s ability to understand, retain and weigh information about whether to participate, the person with Down syndrome will be asked to say what they think the study is about and what it will involve if they take part. Individual informed consent will then be obtained from persons who demonstrate that they have a good grasp of the study and understand that they can choose whether to take part. For persons considered not to have full decision-making capacity to consent to participate in the trial, the informed consent of their legal representative, as defined in the Medicines for Human Use (Clinical Trials) Regulations 2004 (CTR), will be sought. A separate information sheet will be used with relatives and other legal representatives for this purpose. Participation in the qualitative component of the study will require a separate consent. The legal requirement for this in Scotland is to adhere to the Adults with Incapacity (Scotland) Act, 2000. Hence, capacity to consent is assessed as outlined above. Persons then consent for themselves if they have the decision-making capacity to do so; otherwise, consent is obtained from their welfare guardian or nearest relative (as defined in the Act).

### Statistical power

Approximately 60 participants with Down syndrome ages 50 and older will be randomized. Recruitment feasibility will be assessed on the bases of the number of people identified per 10,000 population and the percentages of those contacted who would like to participate, and, among those, the percentage who are eligible to participate. For example, if 200 individuals are contacted and 100 agree to be screened, from among whom 60 are eligible for randomization, then the overall recruitment rate will be 30% with a 90% confidence interval (CI) of 25% to 36%. This will be sufficiently accurate to allow planning for a larger RCT. Similarly, if 50 participants complete the 12-month follow-up, the retention rate will be 83% with a 90% CI of 73% to 91%.

The variance of the rate of cognitive decline will be estimated to calculate the sample size required for a definitive RCT. The precision of this estimate is a function of the sample size in this pilot study. We think that a sample size of 50 participants from whom we gather 12-month outcome data is appropriate at this stage to provide a variance estimate that is reasonably precise, without requiring that we recruit an excessively large sample. With 50 participants, a 90% CI for the variance in the rate of cognitive decline will have a width of approximately 70% of the estimated variance. A smaller sample size in this pilot study would greatly increase the uncertainty in the variance estimate, whereas calculation of a more precise estimate could require considerably more participants. For example, halving the width of the 90% CI for the estimated variance would require 180 participants, which we believe is too large for a pilot study designed to show the feasibility of an RCT.

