**Figure 1 F1:**
[figure not shown]
**Flowchart of the study protocol.** AE, Adverse event; APO E, apolipoprotein E; AR, Adverse reaction; CYP3A4, Cytochrome P450 3A4; GG&C, NHS Greater Glasgow & Clyde; OD, Once daily; RCT, Randomized controlled trial; SAR, Serious adverse reaction.

1. The study will be randomized to determine if, in this population, participants and caregivers are willing to receive the intervention or placebo without knowing which is being administered. Randomization will be stratified for baseline characteristics known to influence cognitive decline (age <55 and ≥55 years and ApoE e4 genotype) or characteristicswhere there is some limited evidence of influence (cholesterol <5 mmol/L and ≥5 mmol/L) to prevent any imbalance in participant types between treatment groups.

2. Semistructured interviews will be conducted with participant-caregiver dyads to gain an understanding of their views on their decision whether to participate and be randomized, and their assessment experiences.

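### The definitive trial is to be sized on the variance of 12-month cognitive decline, with the baseline score and the three randomisation factors used only in side analyses; a baseline-adjusted residual variance is generally the more efficient planning figure

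*Protocol article*

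**What the plan says.** The section Statistical power names the planning quantity: "The variance of the rate of cognitive decline will be estimated to calculate the sample size required for a definitive RCT". It justifies the pilot's size by the precision of that quantity: "We think that a sample size of 50 participants from whom we gather 12-month outcome data is appropriate at this stage". The precision claimed at that size is that "a 90% CI for the variance in the rate of cognitive decline will have a width of approximately 70% of the estimated variance", and the section adds that "halving the width of the 90% CI for the estimated variance would require 180 participants".

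Under Data analysis, Pilot randomized controlled trial, the interest in the treatment comparison is said to lie less in its magnitude or significance, "rather regarding the uncertainty in this estimate or the variability in the rate of cognitive decline from which this estimate is derived". The text continues: "It is this variability estimate that will inform the sample size for a definitive trial, along with information about likely recruitment and retention rates".

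Research questions 3 and 5 place the cognitive tests at baseline and after 12 months, with no other time point.

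On allocation, the text below Figure 1 says: "Randomization will be stratified for baseline characteristics known to influence cognitive decline". It names age (below 55, or 55 and over) and ApoE e4 as known influences, and cholesterol (below 5, or 5 mmol/L and over) as one with limited evidence. In the analysis section these factors and baseline cognitive function are named only in supplementary analyses of decline, whose stated use is to help define the target population of later studies. The same section defers detail to a statistical analysis plan to be written before unblinding. It also says that the definitive sample size will be estimated under alternative assumptions.

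**The concern.** With two time points, analysing change is the same as analysing the 12-month score with the baseline slope fixed at 1. Estimating the slope instead can only lower the residual variance, apart from the degrees of freedom used. Where the stratification factors predict decline, leaving them out of the model also gives a conservative standard error for the arm difference.

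The planning variance is a main product of this pilot. Under Research question 7, recruitment and completion rates and the effect estimate with its uncertainty determine the general population pool, and the pilot is also to consider the recruiting area and its cost. The Discussion describes recruitment of adults with intellectual disabilities as notoriously hard. If the definitive trial were sized on the change variance alone, it might ask for more participants than an adjusted analysis needs, although every variable for the adjusted figure is already collected.

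**Working it through.** **1. The protocol's own precision figures.** For a 90% chi-square interval for a variance on d degrees of freedom, the width relative to the estimate is d/χ²(0.05, d) − d/χ²(0.95, d).

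| Model (50 completers) | d | Relative width | Participants needed to halve it |
|---|---|---|---|
| One overall variance | 49 | 49/33.93 − 49/66.34 = 0.706 | 181 |
| Pooled within two arms | 48 | 48/33.10 − 48/65.17 = 0.714 | 178 |
| Arm, baseline score, three factors | 44 | 44/29.79 − 44/60.48 = 0.750 | 166 |

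The stated width of about 70% and the stated 180 reproduce with the first two rows. They fit the third less well. This suggests a variance without covariates but does not prove it.

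**2. Change variance against adjusted variance, equal SDs.** Let σ be the SD at each time and ρ the baseline-to-12-month correlation (assumed; the documents give none).

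- Change: 2σ²(1 − ρ)
- Residual after baseline adjustment: σ²(1 − ρ²)
- Ratio, adjusted to change: (1 + ρ)/2

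| ρ | Change/σ² | Adjusted/σ² | Ratio | Reduction | Excess n if sized on change |
|---|---|---|---|---|---|
| 0.5 | 1.00 | 0.75 | 0.75 | 25% | 33% |
| 0.7 | 0.60 | 0.51 | 0.85 | 15% | 18% |
| 0.8 | 0.40 | 0.36 | 0.90 | 10% | 11% |
| 0.9 | 0.20 | 0.19 | 0.95 | 5% | 5% |

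The last column is 1/ratio − 1, because sample size is proportional to variance for a fixed difference.

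**3. Sensitivity to unequal SDs.** If the follow-up SD is k times the baseline SD, the ratio is k²(1 − ρ²)/(1 + k² − 2kρ). With k = 1.2 (assumed):

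- ρ = 0.5: 1.080/1.240 = 0.871, a reduction of 13%
- ρ = 0.7: 0.734/0.760 = 0.966, a reduction of 3%
- ρ = 0.8: 0.5184/0.5200 = 0.997, a reduction of 0.3%
- ρ = 0.9: 0.2736/0.2800 = 0.977, a reduction of 2%

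The gain is nil where kρ = 1 (here ρ = 0.83), because the fitted slope is then exactly 1.

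**4. The pilot's interval for the arm difference (25 per arm, equal SDs).** These are 90% half-widths relative to the change-score analysis. Residual degrees of freedom are 48 for change, 47 with baseline, and 44 with baseline and three factors. Chance covariate imbalance is allowed for by multiplying the variance by 1 + 1/46 or 1 + 4/44.

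| ρ | Baseline only | Baseline plus three factors that explain nothing |
|---|---|---|
| 0.5 | 0.88 | 0.91 |
| 0.7 | 0.93 | 0.96 |
| 0.8 | 0.96 | 0.99 |
| 0.9 | 0.99 | 1.02 |

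The last column treats the factors as balanced only by chance, which is pessimistic after stratified randomisation. If the factors explained a further 5% to 20% of the residual variance (assumed), the required sample size would fall by a further 5% to 20%.

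**The case against.** The strongest reply is that covariate adjustment belongs in the statistical analysis plan, which the protocol promises and which is not shown. This has force. A reader might infer that the protocol commits itself to an unadjusted comparison of raw change. It does not: no sentence calls the analysis raw or unadjusted, and regressing change on arm and baseline gives the same arm effect and residual variance as modelling the 12-month score. What remains is that the protocol itself names the planning quantity, that its precision figures fit a variance without covariates, and that baseline cognition and the factors are given a different purpose.

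A reader might also infer that the definitive trial will be too large. The protocol computes no definitive sample size, offers alternative assumptions, and gives no correlation from which to size an excess. Any error is conservative: it protects power and causes no bias.

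Nor does it follow that the pilot's intervals in general are too wide. Recruitment and retention intervals do not depend on this choice, and the interval for the variance becomes slightly wider in relative terms under adjustment. Only the interval for the arm difference could narrow, and not in every case. The benefit from the factors depends on their predicting outcome, and the protocol itself claims only limited evidence for cholesterol.

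Finally, the supplementary analyses would show how strongly baseline and the factors relate to decline. That partly meets the point, but nothing links their result to the planning variance.

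**Conclusion.** The point holds as a question of efficiency, not of error. The protocol names the variance of 12-month decline as the figure that sizes the definitive trial and does not connect the baseline score or its own stratification factors to it. No stated number is wrong.

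The size of the gain is uncertain. With equal SDs it is 25% to 5% of the variance over assumed correlations of 0.5 to 0.9. With a follow-up SD 1.2 times baseline it is about 13% at 0.5 and at most about 3% at 0.7 to 0.9. A material saving therefore needs a moderate or low correlation, which only the pilot data can show. The change is still worth making because the data are already collected and its cost is small.

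**What to change.** In the analysis plan, and in the protocol's description of the planning quantity, state that for each cognitive outcome:

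- The arm difference and its 90% CI come from a linear model of the 12-month score on arm, baseline score, age group, ApoE e4 and cholesterol group.
- The residual variance of that model, with its 90% CI, is the main planning variance for the definitive trial.
- The change-score variance and the observed baseline-to-12-month correlation are reported beside it, as one of the alternative assumptions already foreseen.

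The change is one of wording and needs no new data. It uses about 4 of 48 residual degrees of freedom, so the relative width of the 90% CI for the variance rises from about 0.71 to 0.75. The interval for the arm difference may widen by about 2% if the correlation is near 0.9 and the factors explain nothing. If the unseen analysis plan already contains this model, all that is needed is to bring the protocol's planning quantity into line with it.
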